#### Qualitative data collection

In order to both produce a comprehensive picture of the mechanisms underlying the impact of the intervention on the household and PLWH, and to assess the feasibility and acceptability of the household intervention, different qualitative data sources are employed, namely focus group discussions with the CHWs and repeated in-depth interviews with PLWH in the intervention arm and interviews with household members who voluntarily took part in the intervention visits. These various qualitative research methods allow examination of the same topic from different angles, achieving data triangulation and improving validity of results [35].

In-depth interviews are used to reveal the internal dynamics of the household and the acceptability of the household intervention. A sample is drawn of approximately 15 PLWH in the intervention arm. This number is indicative, as qualitative data collection will continue until saturation has been reached. In addition, for each PLWH who participates, one household member (who voluntarily participated in the intervention) is invited for an interview. Using a semistructured interview guide, longitudinal in-depth interviews with the selected respondents will be conducted at three different time points: before the start of the intervention (month 0); in the middle of the intervention (month 6); and at the end of the intervention (month 12). Longitudinal qualitative data collection allows assessment of the changing dynamics within and outside the household that influence HIV competency, as well as its impact on PLWH and their (un)infected household members. The topics explored during the qualitative interview include HIV testing, stigma, disclosure, treatment adherence support, household support, and aspects of HIV competence. All interviews are conducted in the native language of the respondents (isiXhosa, Afrikaans or English).

Furthermore, all CHWs delivering the intervention are invited to participate in a focus group discussion to assess the feasibility of the intervention. The perceptions of those delivering the intervention are valuable because they may have important divergent insights into the way in which the intervention works to change HIV competence levels. The focus group discussions are conducted with all CHWs in their preferred language (isiXhosa, Afrikaans or English).

### Data processing and management

All quantitative and qualitative data will be anonymised and stored on a secure server. The list with the names of the respondents and their corresponding respondent numbers will be stored safely in a locked cabinet in the office of a School of Public Health or University of Antwerp researcher. The participant list will only be used for the purpose of identifying the follow-up respondents. This list with respondent names will be kept separate from the quantitative and qualitative databases. All these data will be kept for 5 years after the completion of the study.

#### Quantitative data processing and management

The quantitative data collection is guided by the mobile application Mobenzi. The Mobenzi servers are hosted in private subnets of the Amazon Web Service, where security group filters and network access control lists are utilised within a virtual private network (VPN) environment to ensure data security. Completed quantitative surveys are periodically uploaded and removed from the fieldworkers’ devices once the server acknowledges its receipt. Data are encrypted in transit using Secure Sockets Layer (SSL) [34].

#### Qualitative data processing and management

The qualitative in-depth interviews with PLWH and the focus group discussions with the CHWs delivering the intervention will be recorded. These data will be captured and analysed so that the anonymity of the respondents is maintained. Each respondent will be given a unique identifier. The coding sheet with all respondent numbers (identifiers) will be stored on a secure campus server. The audience will thus not be able to link individual statements to particular focus group participants and interviewees. If any statements would potentially reveal the identity of a respondent (e.g. because the respondent gives information specific to a certain household or patient), the research team will not include this statement so as to protect their identity.

### Data analyses

#### Quantitative data analysis

The comparison between the two arms using cluster-specific analysis techniques will allow us to assess the net impact of the household intervention on both the primary and secondary outcomes. First, we will perform an intent-to-treat analysis. In a second step, an analysis based on dose-response data will be conducted.

Furthermore, the main relationships between the relevant concepts (household intervention, HIV competence, prevention and treatment outcomes) will be analysed using latent cross-lagged modelling (Mplus). Using chi-square difference testing [36], measurement invariance will be tested to assess whether the latent factors are fully scalar invariant over time (pre- and postintervention). The latent factors will be modelled accordingly in the structural models over time [37]. The analyses will control for demographic and social characteristics, and the medical and medication history of the patient. Furthermore, other quantitative data analysis methods will be used to analyse the baseline and follow-up quantitative data, such as latent cross-lagged modelling, multilevel modelling, logistic regression and Poisson regression, among others. In this way, these results will allow us to successfully reach our research aims, namely to develop and scientifically test the impact of a household intervention on ART outcomes. No missing data are to be expected because of the nature of the Mobenzi data collection tool. To monitor the attrition between the first and second wave, an attrition analysis will be conducted.

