### Research aims

In this project, the HIV competent household concept will be advanced beyond the merely theoretical and conceptual level. Building on the existing literature and our preparatory work, the current project aims to investigate empirically to what extent and in what way HIV competent households can become sustainable health-enabling contexts that can provide an answer to the HIV prevention and treatment challenges facing South Africa. To this end, this project—the *Sinako* (‘we can’ in isiXhosa) HIV and households study—aims to test an evidence-based household intervention delivered by CHWs to: 1) increase HIV competence in PLWH and their households; and subsequently 2) optimise the impact of CHW support on individual antiretroviral treatment outcomes.

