### Outcomes

In order to assess the impact of the intervention, key baseline assessment indicators are considered. These include primary and secondary outcomes (Table 2). As the current study aims to optimise the impact of CHW support on individual ART outcomes by stimulating HIV competent households, the primary outcomes for this study are: 1) patient’s viral load and 2) ART adherence (measured by the Adherence to Combination Therapy Questionnaire [31]). Data on ART adherence is collected from the enrolled individual by the research team. In addition, departmental permission has been requested to access the viral load data already collected by the Department of Health. As such, this study only requires secondary access; viral loads will not be collected by the research team.

**Table 2 Tab2:** Outcomes for pre- and postintervention assessment

Primary outcomes	
• Viral load	
• Adherence to antiretroviral treatment	
Secondary outcomes	
Individual-level:	
• HIV knowledge	
• Condom use	
• Quality of life	
• Self-management	
• Disclosure	
• Perceived social support	
Household/-level:	
• HIV knowledge	
• Condom use	
• HIV-related stigma	
• Communication about HIV	
• Household functioning	
• HIV testing	
• Support to a household member living with HIV	

*HIV* human immunodeficiency virus

Moreover, we assess the impact of our intervention on a range of secondary process-related outcomes, measuring both individual outcomes and aspects of HIV competence of the households, which should facilitate individual ART adherence (and thus support the primary outcomes). At the individual level, the PLWH questionnaire assesses HIV knowledge, condom use, quality of life, self-management, perceived social support and disclosure. Outcomes measured at the household level include HIV knowledge, condom use, HIV-related stigma, communication about HIV, household functioning, HIV testing and support to a household member living with HIV. These outcomes are included as indications of household comfort with HIV and communicating about HIV and could be considered as proxy measures for HIV competency at the household level.

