##### Follow-up data collection

In order to ensure maximum comparability, the postintervention questionnaire collects information on the same outcomes as the baseline questionnaire from the same respondents in both the intervention and control arms of the RCT. The same data gathering procedure will be followed for the post-intervention assessment as for the baseline data collection. If a patient drops out, the research team will try to trace the patient to understand the reason for this loss to follow-up.

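### The two-wave cross-lagged path from HIV competence to ART outcome starts from pre-intervention competence, so it must not be read as evidence that the intervention works through competence

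*Protocol article*

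**What the plan says.** The Research aims describe a sequence. The intervention is to "increase HIV competence in PLWH and their households; and subsequently 2) optimise the impact of CHW support on individual antiretroviral treatment outcomes".

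Under Quantitative data analysis, an intent-to-treat comparison of the arms comes first, followed by a dose-response analysis. The relationships linking intervention, competence and outcomes then "will be analysed using latent cross-lagged modelling (Mplus".

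The quantitative data have two time points. The same section says that "measurement invariance will be tested to assess whether the latent factors are fully scalar invariant over time (pre- and postintervention", and it plans an attrition analysis "To monitor the attrition between the first and second wave". Under Follow-up data collection, "the postintervention questionnaire collects information on the same outcomes as the baseline questionnaire from the same respondents". Table 2, which lists viral load, adherence and the competence proxies together, is captioned "Outcomes for pre- and postintervention assessment".

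The baseline patient interview belongs to the month 1 preparatory visits, and the household member must be interviewed before the first intervention visit. The interviews at months 0, 6 and 12 are qualitative and cover about 15 patients, all in the intervention arm, with an invited household member each.

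For viral load, the Outcomes section says "departmental permission has been requested to access the viral load data already collected by the Department of Health" and "viral loads will not be collected by the research team". No sampling dates are given.

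**The concern.** In a cross-lagged model with two waves, the lagged path from competence to outcome runs from baseline competence to follow-up outcome. Baseline competence predates the intervention and cannot carry its effect. Competence as changed by the intervention is first measured in the same wave as self-reported adherence, so its link with adherence appears only as a residual correlation at that wave.

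If a positive lagged path were taken as support for the HIV-competent-household mechanism, the conclusion would rest on a quantity that is positive even when the intervention has no effect.

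**Working it through.** The protocol gives no figure for this analysis, so there is none to reproduce. All path values below are illustrative assumptions.

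**Model.** Let A be arm, C0 and C1 competence at baseline and follow-up, and Y0 and Y1 the outcome.

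- C1 = a·A + s·C0 + e
- Y1 = d·A + g·C0 + t·Y0 + b·C1 + u

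Here a·b is the effect through competence and d is the direct effect. Substituting C1 gives what the cross-lagged model estimates:

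- Y1 = (d + a·b)·A + (g + b·s)·C0 + t·Y0 + (b·e + u)

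The lagged path is g + b·s. It contains neither a nor d, so the route of the intervention's effect does not enter it. The residual covariance of C1 and Y1 is b·var(e) + cov(e,u).

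**Numbers.** Take s = 0.5, t = 0.3 and var(e) = 1.

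| Scenario | a | b | d | g | var(u) | cov(e,u) | A→C1 | A→Y1 | C0→Y1 | Residual correlation |
|---|---|---|---|---|---|---|---|---|---|---|
| 1. Full mediation | 0.5 | 0.4 | 0 | 0 | 1 | 0 | 0.50 | 0.20 | 0.20 | 0.37 |
| 2. No mediation, independent residuals | 0.5 | 0 | 0.2 | 0.2 | 1 | 0 | 0.50 | 0.20 | 0.20 | 0.00 |
| 3. No mediation, shared influences at follow-up | 0.5 | 0 | 0.2 | 0.2 | 1.16 | 0.4 | 0.50 | 0.20 | 0.20 | 0.37 |
| 4. Intervention does nothing | 0 | 0.4 | 0 | 0 | 1 | 0 | 0.00 | 0.00 | 0.20 | 0.37 |

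In rows 1, 3 and 4 the residual correlation is 0.4/√(1 × 1.16) = 0.37. The lagged path is 0 + 0.4 × 0.5 = 0.20 in rows 1 and 4, and 0.2 + 0 = 0.20 in rows 2 and 3.

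**Mediation model on the same data.** Adding C1 to the outcome equation gives it the coefficient (residual covariance)/var(e). The direct arm effect is then the total effect minus a times that coefficient.

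- Row 1: 0.40, direct 0.20 − 0.5 × 0.40 = 0.00
- Row 2: 0.00, direct 0.20
- Row 3: 0.40, direct 0.00

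Simulating rows 1 and 2 with 200,000 observations each gave a lagged path of 0.201 in both. The coefficient on C1 was 0.406 and 0.003, and the direct arm effect 0.001 and 0.198. Row 3 has no mediation, yet the mediation model shows full mediation.

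**Limit of the invariance.** Rows 2 and 3 set g = 0.2. With b = 0 and g left at 0, the lagged path would be 0. The path does respond to how competence and outcome are related without the intervention. What it does not respond to is how the intervention acts.

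**Check at trial size.** A second set of values used s = 0.5, g = 0.1, b = 0.3, outcome stability 0.4, and a path of 0.1 from Y0 to C1. The simulation had 12 clusters, 360 participants and an intracluster correlation of 0.002 (all from Sampling), with 3,000 runs.

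- The lagged path averaged 0.250 when the arm acted wholly through competence. It also averaged 0.250 when the arm left competence unmoved and acted directly on the outcome.
- Its standard deviation over runs was about 0.045, so the mean lies 0.250/0.045 = 5.6 standard deviations above zero in both cases.
- The arm-to-competence path averaged 0.501 and −0.001 respectively, so that path does tell the two apart.

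**The case against.** A reader might infer that every estimate in the cross-lagged model is the same with and without mediation, and that only a mediation model can tell the two apart. The working does not support that. Between rows 1 and 2 the residual correlation differs (0.37 against 0.00), and it is a standard part of the model. In this linear case the mediation coefficient is that same residual covariance rescaled. Row 3 then shows the mediation model giving the wrong answer when follow-up competence and outcome share unmeasured causes. Its advantage is that it states the quantity of interest and the assumption behind it. It does not remove the need for that assumption.

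A reader might also infer that the trial cannot address its aims. That goes too far. The intent-to-treat comparison covers primary and secondary outcomes, so the effects on competence and on ART outcomes each rest on randomisation. A null arm-to-competence path would count against the chain. Qualitative work is also assigned to the mechanisms, though with only about 15 patients in one arm. The Quantitative data analysis section itself restates the aim as impact on ART outcomes, although the Discussion keeps the sequence.

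Finally, the article gives no path diagram, does not say the lagged path will be read as mechanism, and ends its list of methods openly. That is fair: the misreading is a risk and not a stated intention. What remains is that the article names this model for these relationships, names no mediation analysis, and describes only two survey waves. More detail elsewhere would leave the ordering of competence and survey adherence unchanged.

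**Conclusion.** The point holds as a limit on interpretation. With two waves, the lagged competence-to-outcome path is the same (0.20 in the illustrative models) under full mediation, direct action or no intervention effect, so it cannot support the sequence in the Research aims. The model can refute the chain through a null arm-to-competence path but cannot confirm it. The second-wave residual correlation does not settle the matter, since mediation and shared unmeasured influences each give 0.37.

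This rests on linear, additive intervention effects, on arm being in the model, and on assumed path values. The algebra, not the particular values, carries the conclusion. The plan should be corrected before the mechanism analysis is run. The primary comparison is not touched.

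**What to change.** Make the mechanism analysis an explicit mediation model: arm to follow-up competence to outcome, conditional on baseline competence, baseline outcome and the planned covariates, and allowing for clustering by facility. State that it assumes no unmeasured confounding between follow-up competence and outcome, and report a sensitivity analysis for that assumption. Keep the two-wave cross-lagged paths, labelled descriptive.

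Where routine viral loads dated after the follow-up survey are available, use them in a supporting analysis so that competence is measured before the outcome. Say plainly that this may select patients retained in care and does not remove confounding.

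The main change costs analysis-plan wording and one sensitivity analysis, with no new survey wave. The viral-load analysis also needs a dated extract, probably a later data cut, and would have fewer patients. How many cannot be judged, because the article gives no sampling dates and reports access permission only as requested.

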#### Qualitative data analysis

Data collection and data analysis phases will be alternated to assist subsequent interviews and to assess when data saturation has been reached. After written informed consent is obtained all interviews will be audiotaped, allowing us to produce a detailed transcript of the interviews. These transcripts ensure accuracy of what is said and serve as the basis for data analysis. The recordings of the interviews will be transcribed verbatim and, when necessary, translated into English. A sample number of translations will be back translated into the local language for a quality check. Transcripts will be imported into NVivo. Data will be analysed carefully by reading and re-reading the field notes and transcripts of interviews. Codes for a sample of transcripts will be compared with another researcher’s codes and similarities and differences will be discussed, thus ensuring intercoder reliability. The analysis will be performed in accordance with the Grounded Theory principles described by Strauss and Corbin [38].

### Monitoring

When baseline data become available, descriptive analysis and structural equation modelling using Mplus will be conducted. A special data monitoring committee, made up of delegates from both institutions and external institutes, will be informed on the progress of the trial. This committee is independent from the sponsor and funders. Furthermore, the study will be guided by a steering committee, consisting of the two local principal investigators and a postdoctoral fellow.

A debriefing and internal monitoring plan will be followed to further monitor the intervention progress and to assess quality of delivery. Adverse events resulting from the intervention are reported on the same day to the principal investigator who will report these to the ethics committee of both institutions involved in the study (the University of the Western Cape and the University of Antwerp). However, no extreme adverse events are anticipated. In case psychological support is needed, the research team will provide counselling contacts.

One key to monitoring and evaluation is establishing whether it is ethical to continue the trial. To limit the potential risks for participants, we will organise a mid-term review of the intervention to assess its initial impact. In the unlikely event that the intervention has a negative impact on the health or mental well-being of the participants the trial will be stopped immediately. The project partners (the University of the Western Cape and the University of Antwerp) must mutually decide this in consultation with one another and the ethics committees of both institutions.

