## Methods/design

### Trial design

The primary activity for the Sinako study will be the implementation and assessment of the impact of an HIV competent household intervention. Table 1 represents a schedule of intervention implementation, assessment and dissemination. The intervention will be assessed in a cluster-randomised control trial (RCT) with two arms. CHWs will be the primary actors in this RCT, either continuing to deliver a standard ART adherence support service (arm 1), or a standard ART adherence support service plus a household P^2^CP intervention (arm 2). CHWs, however, are linked to a health care facility, which creates a risk of contamination when CHWs active in different arms operate from the same facility. The facility was therefore selected as the cluster unit of randomisation. The health care facilities in the study setting were categorised as large or small facilities according to the numbers of CHWs employed, which also corresponds to the number of patients. Subsequently, 12 facilities were grouped by selected subdistricts and were randomly selected from the list of facilities for inclusion in the study in arms 1 and – resulting in six facilities or clusters per trial arm. Further blinding of the study arms was not possible because of the clear differences between the intervention and the standard of care. The design and report of this clinical trial protocol follows the Standard Protocol Items: Recommendations for Interventional Trials (SPIRIT) statement (Additional file 1).

**Table 1 Tab1:** Schedule of intervention implementation, assessment and dissemination

	Year 1	Year 2	Year 3	Year 4
Preparatory research activities				
Ethical approval	X			
Preparatory literature review	X			
Quantitative survey development	X			
Mobile data collection tool programming	X			
Qualitative questionnaire development		X		
Development of the household intervention	X	X		
Pilot of the household intervention		X		
Drawing study sample for cluster-RCT		X		
Fieldworker training		X		
Baseline assessment of HIV competence and HIV outcomes				
Baseline quantitative data gathering, capturing and cleaning		X		
Qualitative data collection		X	X	
Baseline quantitative data analysis			X	X
Writing of reports and articles		X	X	X
Implementing the household intervention				
Workshops providing training to CHWs conducting the intervention		X		
Screen participants for eligibility		X		
Informed consent		X		

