#### Implementation of the HIV competent household intervention

The CHWs who are part of the intervention arm received 9 training days with a focus on role play and ensuring that the CHWs understand the intervention and the importance of standardisation of the delivery. At the end of the training, the CHWs were informally assessed to evaluate the grasp of content and technique to deliver the intervention. Furthermore, regular debriefing sessions are planned with the CHWs to monitor compliance with the intended standard of the intervention delivery and to improve adherence to the intervention protocols.

Various strategies are followed to maximise participant retention in the study. First, potential participants who return for follow-up care and treatment visits after the initial diagnosis visit are recruited into the study. Patients who return for follow-up treatment and care portray commitment to their own health betterment and are as such perceived as patients who are likely to commit to long-term participation in the Sinako study. Second, CHWs have been trained to answer pertinent questions about the study that may be posed by potential participants at every opportunity or as and when requested. Third, tailored strategies are used specific to the individual participant. For instance, a potential participant of the Sinako study will, from time to time, travel out of the province. This poses a risk of attrition from the study. To mitigate this risk and improve retention rates, the CHWs have been trained to check with the enrolled patients regarding travelling plans. In addition, the patient is also requested to inform the CHW of such travel, whether planned or occurring as an emergency. Finally, the CHW follow-up visits with the patient or the fieldworker data collection appointment with the household member are, as far as possible, scheduled according to the participants’ convenience. This is to ensure that study activities adapt to participants’ availability and are not imposed. This in turn is intended to improve retention.

If an individual participant does not want to continue participating in the study the intervention for this particular respondent will be stopped. In case of a particular adverse event (e.g. admission to a hospital), the principal investigator will make an informed decision whether or not to continue the trial for this particular participant.

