### Ancillary and post-trial care

There are essentially three groups of participants: 1) HIV patients on ART; 2) household members; and 3) CHWs providing the intervention. Groups 2 and 3 are not exposed to any risks. These participants will share their views and experiences regarding life in the household (group 2) and their work (group 3), respectively.

The PLWH enrolled in the cluster-RCT (group 1) are exposed to two potential risks for which we have developed strategies to prevent and mitigate possible negative effects. First, the patients on ART receiving the standard treatment (CHW support) are not exposed to any potential negative effect. The Non-Governmental Organisation (NGO) providing the CHW support has been providing this support for several years and is accredited and funded by the provincial Department of Health. These trained CHWs have a standard procedure to protect the person living with HIV from any unintended consequences (e.g. the disclosure of their HIV status to the family/community). Patients starting treatment follow counselling sessions at the clinic where they are introduced to their CHW, who then makes an appointment for follow-up support visits (starting with a home assessment to record the social and housing conditions). If the patient does not want the CHW to visit their home, the meetings with the CHW are organised at their preferred location. This standardised procedure has been working for many years and has assisted thousands of HIV patients to commence their treatment. No unintended consequences are therefore expected in this arm. The HIV patients in the intervention arm, however, will be subjected to a household intervention. The intervention is based on the available literature on intervention development and the theoretical frameworks developed in family sociology and psychology [39]. The entire development process also incorporated all relevant stakeholders, namely HIV patients, CHWs, the Department of Health and the City of Cape Town. However, it must be noted that every intervention can have unintended (negative) consequences. When the CHW or fieldworkers deem necessary, they will also provide contact details for relevant referrals to health or social development government services or community-based or NGOs experienced in mitigating negative family dynamics and HIV treatment difficulties.

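### The adverse event reporting rule depends on attribution to the intervention, so its reports give no comparable adverse event data by arm for the mid-term review or the stopping decision

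*Protocol article*

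**What the plan says.** Four parts of the protocol article bear on adverse events.

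- **Monitoring** gives the reporting route: "Adverse events resulting from the intervention are reported on the same day to the principal investigator", who then informs the ethics committees of both universities. The same section promises that "we will organise a mid-term review of the intervention to assess its initial impact", and gives a stopping condition: "In the unlikely event that the intervention has a negative impact on the health or mental well-being of the participants", the trial stops at once.
- **Implementation of the HIV competent household intervention** has a second provision: "In case of a particular adverse event (e.g. admission to a hospital), the principal investigator will make an informed decision" on whether that participant goes on in the trial. It names no arm and sets no condition on cause.
- **Ancillary and post-trial care** treats the arms differently. Of standard support it says: "No unintended consequences are therefore expected in this arm". Of the intervention arm it says that "it must be noted that every intervention can have unintended (negative) consequences". Of household members and community health workers (CHWs) it says: "Groups 2 and 3 are not exposed to any risks".
- **Trial design** says that the arms are known: "Further blinding of the study arms was not possible because of the clear differences between the intervention and the standard of care".

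**The concern.** The wording under Monitoring makes a causal judgement the entry condition for a report. A control participant receives no study intervention. Taken literally, an unwanted disclosure, a household conflict or an admission in that arm would not qualify under this rule, while the same event in the intervention arm might. The article does not say who makes the attribution, but with open arms whoever makes it can know the allocation.

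What is at stake is the use of these reports. The stopping condition asks whether the intervention causes harm. Participants have just started or restarted treatment, so some admissions and distress can be expected in either arm. A count from the intervention arm with no control count beside it cannot separate background events from harm done by an intervention that encourages disclosure.

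**Working it through.** The article states no event rate, event count or safety test, so there is no figure to reproduce. The check sets the provisions side by side.

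1. **Does the reporting rule treat the arms alike?** Its condition is that the event results from the intervention. Under Intervention visits (months 2–8), control participants get the standard package, a pill count. Read literally, the condition can be met only in the intervention arm.

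2. **Is the control arm in fact free of such events?** The article does not show this. Control participants also receive CHW visits, a home assessment and, where it can be arranged, an interview with a household member. Ancillary and post-trial care itself names disclosure of HIV status to family or community as something that the CHWs' standard procedure has to guard against. It also treats non-disclosure to the household as a risk for participating patients without limiting this to one arm.

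3. **Do the two adverse event provisions agree?** They do not match. Monitoring asks for attribution. The implementation section refers to an event such as hospital admission with no attribution and no arm. The second provision concerns whether one participant continues, and sets no recording or reporting by arm. A CHW who learns of an admission in a control participant could not tell from the two texts whether it should be reported and through which route.

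4. **Do other data fill the gap?** In part. Table 2 lists viral load, adherence, quality of life, disclosure, HIV-related stigma and household functioning. Follow-up data collection gathers the same outcomes in both arms, and the quantitative analysis compares the arms by intention to treat. Two limits remain. The surveys are taken before and after the intervention, so they may not serve a mid-term review. And Table 2 does not list admission, death, household violence or unwanted disclosure. Disclosure is listed, but the intervention promotes it, and the name of the measure does not separate voluntary from harmful disclosure.

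5. **Is the statement about household members consistent?** Ancillary and post-trial care says they face no risk because they only share their views. Intervention visits (months 2–8) has household members and sexual partners join sessions and take part in the activities, and Qualitative data collection counts session attendees among those interviewed. The section on HIV competent households warns that a household can be stigmatising and can impede health. These statements do not fit together.

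**The case against.** A reader might infer that events are reported only if attributed, that the control arm can contribute none, and that harm cannot be compared between arms. The documents do not support these stronger readings.

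- The word only is not in the text. The sentence sets a same-day route to the principal investigator and the ethics committees. Expediting related events is compatible with wider routine recording.
- The implementation section lets an event such as hospital admission reach the principal investigator from either arm.
- Harm that shows in viral load, adherence, quality of life, stigma or household functioning can be compared from data collected alike in both arms. Patients who drop out are traced for the reason, with no restriction by arm, so some deaths and withdrawals may come to light in both.
- The article condenses a full protocol and refers to an internal monitoring plan, neither of which is shown. Event lists, forms and the content of committee reports may stand there, and their absence here is no fault.

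All of this stands, and it narrows the point. It does not remove it. The condition on attribution and the presumption about the control arm are stated, not merely left out. The two adverse event provisions differ on the page. Outcome surveys taken after the intervention are not a substitute for event data at a mid-term review.

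**Conclusion.** The point holds in limited form. The reporting rule under Monitoring is conditional on attribution to the intervention, and the control arm is presumed free of unintended consequences. Reports under that rule do not by themselves supply comparable adverse event data by arm for the mid-term review or for a stopping condition that is itself causal. The rule also does not match the unrestricted wording in the implementation section.

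No numerical size can be given. Any figure would need an assumed event rate and an assumed share of events attributed, and the article plans no between-arm test of these reports. The conclusion rests on a literal reading of the reporting sentence and would weaken if the full protocol or the monitoring plan already records events in both arms regardless of cause. It does not extend to the outcomes measured in both arms, where a harmful effect can still be seen. The change is worth making but does not threaten the primary comparison.

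**What to change.** Reword the reporting sentence under Monitoring so that a short, fixed list of events is recorded in both arms regardless of presumed cause: death, hospital admission, unwanted disclosure, household conflict or violence, and distress needing referral. Then:

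- Use identical prompts in both arms, chiefly in the fieldworker follow-up questionnaire. CHW contact differs between the arms (seven structured sessions plus catch-up visits against a pill count), so prompts at CHW visits alone would detect events unequally.
- Record relatedness to the intervention as a separate field. Same-day reporting of related events can stay as it is.
- Give counts by arm to the data monitoring committee, including in time for the mid-term review. Since the follow-up questionnaire comes after the intervention, events learned of during visits in either arm should go on the same form.
- Reconcile Monitoring, the implementation section and Ancillary and post-trial care, including the statement that household members face no risk although they join sessions. Any recording for household members must not reveal the patient's status.

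This concerns what is recorded and reported. It proposes no change to when a participant or the trial should stop.

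The cost is a few questionnaire items on the device already in use, a short form, slightly longer interviews and more events to process. Some difference in detection between the arms will remain because CHW contact differs, and the counts should be read with that in mind.
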